**Figure 1 f01:**
[figure not shown]
Protocol that will be applied. A) Sequence of the data acquisition and group allocation. B) Noninvasive brain stimulation protocol. atDCS = anodal transcranial direct current stimulation; AE = adverse effects; iTBS = intermittent Theta-burst stimulation; min = minutes; MRI = magnetic resonance imaging; SPECT = single photon emission computed tomography.

VAS and salivary cortisol will be collected immediately after the end of the session. For the VAS scale, participants will be asked to manually indicate on horizontal 10 cm lines whether they are experiencing any current pain. ‘Zero’ means ‘no pain’ and ‘ten’ means ‘pain as bad as it could possibly be’. To ensure the safety of both NIBS techniques alone and their combination, an Adverse Effects Scale^33^ will be assessed. This scale consists of identifying the produced effects and measuring them on a scale from 1 to 4 points, being 1 – absent, 2 – mild, 3 – moderate and 4 – severe. The working memory task (n-back) will be applied after measurement of adverse effects.

All of the procedures described above will take place at the Institute of Psychiatry - HCFMUSP. However, after the end of the working memory task, the volunteers will be taken to the Nuclear Medicine Center - HCFMUSP, where the SPECT images will be acquired by a trained team.

### SPECT

Volunteers will be asked to fast 6 hours prior to the SPECT exam. Initially, an injection of the 99mTc-ECD radiotracer with activity of 20 mCi (555 MBq) will be administered during the NIBS session. Images will be acquired up to 60 minutes after administration in SPECT equipment (630 model GE, Milwaukee, WI, USA) consisting of a dual-head gamma camera with dedicated collimator for brain studies (Fan beam). SPECT images will be acquired sequentially with a standardized protocol using a 2.5x zoom factor, 128 x 128 matrix, and acquisition of 240 3/3° projections (two 360° turns) every 20 seconds. The photopic will be centered at 140keV, with a window at 10%. Processing will be performed using an interactive reconstruction method (OSEM) with Butterworth filter, with a cutoff frequency of 0.57, and serial number of 10. The number of interactions used will be 20, with 40 subsets. In addition, we will use the T1 and T2 sequences to correct the data for partial volume effects.

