### Procedure

At the beginning of the study, participants will be screened for participation and asked to give written informed consent. The study is in accordance with the Declaration of Helsinki and was approved by the Ethics Committee at the São Paulo University Hospital das Clínicas (HCFMUSP) and registered on the Plataforma Brasil database (CAAE: 89310918.8.0000.0068).

Participants will be randomized in accordance with a computer-generated list at www.randomizer.org and allocation will be conducted by an assistant not involved in the project. Participants will be asked to come to the research center five times. In line with previous studies of (non)combined NIBS protocols, there will be a one-week interval between the sessions to ensure elimination of carryover effects.^20^ On the first day, all participants will undergo a 3 Tesla MRI (GE, 750W system integrated within a 3.0 Tesla General Electric PET/MRI scanner) scan during which we will acquire T1-weighted and T2-weighted sequences (repetition time [RT] = 1900 ms, echo time [ET] = 2.2 ms, flip angle = 9°, 176 slices/volume, slice thickness = 0.8 mm). MRI acquisition is performed beforehand to target the right and left DLPFC via a neuronavigation system (Brainsight, Rogue Resolutions, Inc). Both left and right DLPFC will be located in each participant by reverse coregistration from the MNI152 stereotaxic coordinates (x - 38, y + 44, z + 26 and x + 38, y + 44, z + 26, respectively) and marked on a cap. This method has been identified as optimal on the basis of clinical outcomes and whole brain functional connectivity.^30 , 31^ After neuronavigation, all other sessions will take place in a well-controlled laboratory environment at the Institute of Psychiatry - HCFMUSP, São Paulo, Brazil. The same procedures will be applied in each of the four sessions, except for neuronavigation, which will only be conducted during the first session.

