Before the start of each of the four experimental sessions, participants will be asked to answer a few baseline measurements such as the HAMD, BDI, PANAS, and Hamilton Anxiety Inventory (HAI) and a visual analogue scale (VAS). These will essentially be applied to identify participants’ brain state before the NIBS session and can also serve as potential moderators of the NIBS effects. Afterward, the volunteers’ resting motor threshold^32^ will be determined using a MagVenture device (MagPro X100, Denmark) and a figure of eight coil. Salivary cortisol will be collected after the motor threshold measurement and before venous access is obtained for administration of the 99mTc-ECD radiotracer. After venous access, subjects will undergo a neurostimulation session ( Figure 1A ). First, the tDCS device will be switched on. The tDCS session will last 20 minutes. However, the tDCS protocol will be applied alone for the first eleven minutes and then, for the last 9 minutes of the neurostimulation session, the iTBS protocol over the left DLPFC will be applied concomitantly. The radiotracer (99mTC-ECD) will be injected right after the start of the iTBS protocol ( Figure 1B ).

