### Statistical analyses

Sample size was calculated using G*Power 3.1 software.^38^ Since this is an original study and no a-priori power analysis is provided, we estimate a moderate *f* – size effect (0.25). The analysis considered four groups, 4 measurements, correlation between repeated measures of 0.5, alpha of 0.05 and power of 0.85, resulting in a sample size of 28 participants. Considering possible losses, we estimate recruitment of 30 subjects (120 observations).

The Shapiro-Wilk test will be applied to identify the sample distribution. Assuming a normal sample, we will perform analysis of variance (ANOVA) having ‘group’ as independent variable and ‘area of activation’ (observed in the left DLPFC) as dependent variable. The Kruskal-Wallis test will be performed in case of a non-parametric sample. The SPECT images will be available in orthogonal cuts in the transverse, sagittal, and coronal planes (DICOM format). Images will be analyzed using the Statistical Parametric Mapping software (SPM12; Wellcome Department of Imaging Neuroscience, London, UK), executed in Matlab Version 2020 (MathWorks, Natick, MA). We will use SPM to form a statistical map according to the statistical threshold to identify differences among the groups. In-house scripts will be used for partial volume correction procedures based on structural MRI. The SPM images will be subtracted from each group to verify areas of functional activation.

ANOVA or its non-parametric extension will be applied for n-back and salivary cortisol, with ‘group’ as independent variable for both outcomes and ‘cortisol level’ (for salivary cortisol) and accuracy/response time (for working memory performance) as ‘dependent variables’. The associations between n-back task performance (accuracy and response time)/salivary cortisol level and cerebral activation will be estimated with linear regression. We will perform pathway analyses to verify whether cerebral activation is directly associated with the results of working memory performance and cortisol salivary level or is measured by these findings. We will also statistically investigate the possible learning effects of the repetitive application of the working memory task by grouping participants’ scores according to the chronological order of NIBS intervention assignments.

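### The radiotracer activity is given in two units that do not agree: 20 mCi is 740 MBq, and 555 MBq is 15 mCi

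*Protocol article*

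**What the plan says.** The SPECT section gives the amount injected: "an injection of the 99mTc-ECD radiotracer with activity of 20 mCi (555 MBq) will be administered during the NIBS session". The figure in brackets reads as the same activity in the second unit. The sentence does not offer it as a range, a minimum, or an activity at a different time.

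The Procedure section makes the injection part of the stimulation session: "The radiotracer (99mTC-ECD) will be injected right after the start of the iTBS protocol". It also says how sessions relate to one another: "The same procedures will be applied in each of the four sessions, except for neuronavigation, which will only be conducted during the first session". Taken together, these mean one injection per session and four per participant. The Statistical analyses section plans for 30 participants and 120 observations.

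The abstract, the Procedure section, the caption of Figure 1 and the Discussion mention the tracer or the scan but give no activity. The sentence in the SPECT section is the only place in the article that does.

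**The concern.** The millicurie and the megabecquerel are linked by a fixed conversion, so an activity given in both units can be checked exactly. This pair fails the check, and by too much for rounding to explain.

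What is at stake is how clearly participant exposure is stated. The volunteers are healthy people who, on the article's description, are injected four times. Anyone who works out their exposure from this sentence gets a different answer depending on the unit used. Anyone who wants to repeat or appraise the imaging meets the same difficulty. The article does state the activity, so this is a contradiction in the text and not a detail left to a fuller document.

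**Working it through.** Inputs:

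- Stated activity: 20 mCi, given as 555 MBq (SPECT section).
- Injections per participant: 4, one in each experimental session (Procedure section).
- Participants: 30, with 120 observations (Statistical analyses section).
- Conversion: 1 mCi = 37 MBq, by definition of the units.

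**Step 1: try to reproduce the printed pair.** 20 × 37 = 740 MBq, not 555 MBq. In the other direction, 555 / 37 = 15.0 mCi, not 20 mCi. The pair is not reproduced either way.

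**Step 2: could it be rounding?** The printed pair implies 555 / 20 = 27.75 MBq per mCi, against a true factor of 37. Both reverse conversions give whole numbers (740 and 15), so nothing is left over for rounding to absorb. It also means that each printed figure could be the intended one and the other the slip. The arithmetic does not favour either.

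**Step 3: size per injection.**

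- Difference: 740 − 555 = 185 MBq, or 20 − 15 = 5 mCi.
- Relative to the lower figure: 185 / 555 = 33.3%.
- Relative to the higher figure: 185 / 740 = 25.0%.

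**Step 4: size over the four sessions.**

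| Figure taken as intended | Per injection | Four sessions |
|---|---|---|
| 20 mCi | 740 MBq | 4 × 740 = 2960 MBq (80 mCi) |
| 555 MBq | 555 MBq (15 mCi) | 4 × 555 = 2220 MBq (60 mCi) |
| Difference | 185 MBq (5 mCi) | 740 MBq (20 mCi) |

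**Step 5: how much of the trial rests on the sentence.** 30 participants × 4 sessions = 120, which matches the planned number of observations. Every planned scan follows an injection whose activity is set by this one sentence.

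**The case against.** The strongest reply is that this may be only a conversion slip in a journal article. One activity may have been fixed in the full protocol or the nuclear medicine order and used throughout. The article reports ethics approval, and the document that was approved is not shown. This reply stands as far as it goes: the text does not show that two activities are in use. It does not remove the contradiction, because the article states the activity and states it inconsistently.

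A reader might infer something stronger: that staff could use one unit in some sessions and the other unit in others, so that image noise differs between conditions within a participant. If activity did vary in this way, and if counts scaled with activity, relative count noise would differ by a factor of √(740/555) = √1.333 = 1.155, or about 15%. The article does not support that inference. It says that the same procedures apply in every session, describes image acquisition as standardised and assigns it to a trained team. If one activity is used throughout, whichever it is, the misprint creates no difference between conditions. The article also describes the order of the stimulation protocols as randomised and counterbalanced, so variation unrelated to condition would add noise and not a systematic shift. The 15% is therefore hypothetical and is not part of this point.

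It is also fair to object that the article gives no dosimetry or exposure limit against which to set 2960 or 2220 MBq. That is correct, and no claim is made that either total is too high or too low.

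**Conclusion.** The point holds. The only statement of the radiotracer activity contradicts itself by 185 MBq (5 mCi) per injection, which is 33% of the lower figure or 25% of the higher. Over four sessions the totals are 2960 against 2220 MBq per participant.

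The size rests on the definition of the units and on reading the Procedure section as one injection per session. The contradiction itself needs only the first of these.

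The consequence is limited to ambiguity in the stated exposure of healthy volunteers and in a parameter of the imaging. The design, randomisation, sample size and planned comparisons are unaffected. The document does not show which figure was intended. It is worth correcting because it concerns radioactivity given to healthy people and the arithmetic leaves no doubt that the sentence is wrong as written.

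**What to change.** Reconcile the two figures against the ethics-approved protocol. Then state one activity in the SPECT section, with a correct conversion if both units are kept. Confirm that any dosimetry and participant information used the same value. Which figure is right is for the sponsor to establish from the approved documents.

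The cost is a one-line correction and a check against documents that the sponsor should already hold. No change to the design or the analysis is needed. Operating details, such as a tolerance around the activity or a record of the activity measured at each session, commonly sit in the full protocol. Their absence from the article is not part of this point.

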### NIBS protocols

Based on previous studies with healthy volunteers^34^ and depressed patients^13 , 14^ using tDCS, the anode will be placed on the left and the cathode over the right DLPFC cortices (bilateral montage), according to the neuronavigation coordinates. A current of 2mA will be applied using 25cm^2^ saline-soaked sponges. All sessions will last 20 minutes and will be performed using a Neuroconn DC-Stimulator MR device (Neuroconn GmBH, Ilmenau, Alemanha) that has a “study mode” and allows for automatic double-blinding according to an imputed code. The sham protocol will consist of a brief active period of 30 seconds fade-in and 30 seconds fade-out at the beginning and end of the session. The randomized codes for all four sessions for both tDCS and iTBS interventions will be stored in sealed, opaque envelopes. Only one person not directly associated with the project will have access to them. For each session, this person will write the codes on a note and deliver it to the technician responsible for the administrations.

ITBS will be performed over the left DLPFC, with a stimulation target located based on neuronavigation. The TMS coil will be placed above the anodal tDCS electrode (coil-scalp-distance: approximately 5mm) and positioned 45 degrees relative to the midline. Stimulation will consist of 54 cycles of 10 triplet bursts with train duration of 2s and an interval of 8s between two successive trains (total of 1620 pulses; Huang et al., 2005^4^ ), at 110% of resting motor threshold. The resting motor threshold will be operationalized as the minimum TMS intensity necessary to visually yield a motor evoked potential in the right abductor pollicis brevis muscle in 5 out of 10 successive attempts.^35^ Based on these parameters, the iTBS protocol will last approximately 9 minutes. All sham and active stimulations will be performed using the MagVenture device. We will employ the Magventure coil (Cool – B65 Active/Placebo), that also has a ‘study mode’, allowing sham or active TMS sessions depending on the numerical imputed code. Thus, from the imputed randomized code, the device will display on the screen which side of the coil should be used. The coil has two identical, symmetrical sides and the sham protocol is additively identical to the active but does not produce electromagnetic pulses.

### Working memory (n-back) task

The n-back will be programmed in E-prime 2.0 software (Psychology Software, Tools Inc Pittsburgh, Pennsylvania, USA). Images will be presented on a 15-inch LCD computer screen and participants will be seated at a distance of approximately 50 cm from the screen. The visual stimulus consists of letters of the alphabet (A to Z) that will appear individually and randomly on the computer screen. Two conditions will be applied, 0-back and 2-back. The tasks will present 3 blocks of 30 letters, each one being displayed on the screen for 500ms, with an interstimulus interval of 3000 ms. A correct response occurs when the subject identifies letter ‘X’ (0-back task) and the same stimuli presented two positions before (2-back task). Response time will also be measured. Higher accuracy values will represent improvement, whereas lower (including negative) response times will represent faster response. This is the same protocol previously used by our group.^8 , 36^

Finally, the n-back task will not be applied before the NIBS session to avoid learning effects. Moreover, n-back performance after the sham protocol will be used as the reference value in our statistical comparison and the randomized and counter-balanced NIBS protocols will allow us to statistically evaluate learning effects by introducing order as a variable in our statistical models. This methodology was applied based on previous studies evaluating working memory performance with NIBS intervention.^37^

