**Methods:**

A randomized, double-blind, sham-controlled, full-factorial design will be conducted. The effects of transcranial direct current stimulation (tDCS) and intermittent theta-burst stimulation (iTBS) will be investigated over four different sessions (sham tDCS + sham iTBS, anodal tDCS + sham iTBS, anodal tDCS + active iTBS and sham tDCS + active iTBS) in 30 healthy adult volunteers. A 99mTc-ethylene cysteine dimer (99mTC-ECD) will be administered during the NIBS session and neuroimaging will be acquired within one hour. Salivary cortisol will be collected before and after each session and an n-back working memory task will be applied after the end of each NIBS session. The outcomes will be cerebral perfusion alterations (99mTC-ECD SPECT), accuracy and reaction time in the n-back task, and changes in salivary cortisol level.

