### Limitations

First, we will not compare the effect of iTBS and cathodal tDCS that have also been shown to increase cortical excitability.^21^ Second, some technical limitations regarding the SPECT exam should be underscored: 1) SPECT measures the CBF, which does not generally exactly reflect brain metabolism, being a better surrogate for brain activity compared with cerebral perfusion; 2) although SPECT is a consolidated neuroimaging method, it presents poorer contrast and spatial resolution when compared to Positron Emission Tomography (PET), for instance; and 3) the within-subject design may introduce learning effects in working memory tasks.

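### Leaving out a pre-stimulation n-back does not avoid learning across four scored sessions; the cost is precision, small if session order is modelled and large if it is not

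*Protocol article*

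**What the plan says.** The n-back section explains why there is no baseline task: "Finally, the n-back task will not be applied before the NIBS session to avoid learning effects". The abstract fixes when the task is given: "an n-back working memory task will be applied after the end of each NIBS session". With four sessions, each person is scored four times.

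The Procedure section sets out the visits: "Participants will be asked to come to the research center five times". The first is the imaging day: "On the first day, all participants will undergo a 3 Tesla MRI". Between the stimulation sessions, "there will be a one-week interval between the sessions to ensure elimination of carryover effects". No n-back or familiarisation run is listed for the imaging day.

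On handling learning, the n-back section adds that "the randomized and counter-balanced NIBS protocols will allow us to statistically evaluate learning effects by introducing order as a variable in our statistical models", and takes performance after sham as the reference. Statistical analyses describes the model differently: "ANOVA or its non-parametric extension will be applied for n-back and salivary cortisol, with ‘group’ as independent variable for both outcomes". There, learning is a separate look at scores grouped by session sequence. Limitations concedes that "the within-subject design may introduce learning effects in working memory tasks".

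**The concern.** Dropping the pre-test removes one extra exposure per session. It leaves four scored exposures a week apart, so the stated reason does not hold for learning between sessions. Without a practice run, the first attempt at the task is itself outcome data. In a balanced order, sham comes first for about a quarter of participants, and for them the reference value is a first attempt.

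At stake is the precision of the condition comparison for accuracy and response time. Learning adds within-person variation in two parts. The average practice curve can be removed by a session term. Differences between people in how much they gain stay in the error term. Which parts remain depends on whether order is in the model, and the two sections do not agree on that.

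**Working it through.** **1. The plan's own figure.** Statistical analyses gives f = 0.25, 4 groups, m = 4 measurements, ρ = 0.5, α = 0.05, power 0.85 and N = 28, with 30 recruited. For the within-subject F test, λ = f²·N·m/(1−ρ).
- N = 28: λ = 0.0625 × 28 × 4 / 0.5 = 14.0. With 3 and 3(28−4) = 72 df, power is 0.878. The next smaller multiple of 4, N = 24, gives 0.813, so 28 reproduces.
- With one group the same formula gives N = 26 (power 0.851).
- N = 30: λ = 15.0, power about 0.90. No sample-size figure is wrong on this point.

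**2. Learning model (assumed).** Person i has a first-exposure deficit L_i ~ N(μ, τ²), in within-person residual SDs. It shrinks to 35%, 12% and 4% at later exposures. One practice run shifts the profile to 35%, 12%, 4% and 1.5%.

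The between-session variance of each profile (divisor 3) sets the cost:
- No practice: mean 1.51/4 = 0.3775; squared deviations sum to 0.5685; variance 0.5685/3 = 0.1895.
- Practice: mean 0.525/4 = 0.13125; squared deviations sum to 0.0698; variance 0.0698/3 = 0.0233.

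With group only, the error variance is multiplied by 1 + (μ² + τ²)·v. With a session term it is multiplied by 1 + τ²·v. λ is 15 divided by that factor.

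**3. Results at N = 30.** The power ranges are from repeated simulations with random order (2,500-4,000 trials per cell; Monte Carlo error about 0.5 points at 4,000).

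| μ, τ | Model | λ, no practice | Power | λ, practice | Power |
|---|---|---|---|---|---|
| 1, 1 | group only | 15/1.379 = 10.88 | 0.79-0.80 | 15/1.047 = 14.33 | 0.89 |
| 2, 1 | group only | 15/1.947 = 7.70 | 0.61-0.62 | 15/1.116 = 13.44 | 0.87 |
| 1, 1 | with session | 15/1.1895 = 12.61 | 0.82-0.84 | 15/1.023 = 14.66 | 0.88-0.89 |
| 2, 1 | with session | 12.61 | 0.82-0.84 | 14.66 | 0.89-0.90 |
| 1, 0.5 | with session | 15/1.0474 = 14.32 | 0.883 | 15/1.0058 = 14.91 | 0.893 |
| 2, 0.5 | with session | 14.32 | 0.876 | 14.91 | 0.893 |
| 1, 0.3 | with session | 15/1.0171 = 14.75 | 0.886 | 15/1.0021 = 14.97 | 0.881 |

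With a session term, practice gains 0-2 points up to τ = 0.5. At τ = 1 the gain is about 4-6 points, with single runs up to 7.

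**4. A second curve, with no person-to-person variation.** Let the total gain from session 1 to 4 be G = 0 / 0.5 / 1.0 / 1.5 total SDs, each step half the one before.
- Group only, random order: power 0.90 / 0.87 / 0.77 / 0.61 without practice and 0.91 / 0.90 / 0.87 / 0.83 with it.
- Group only, 4×4 Latin square, no practice, G = 1.0 and 1.5: power 0.82 and 0.67, so counter-balancing alone does not restore precision.
- Session term in, random order: 0.89-0.91 without practice, 0.89-0.90 with it.

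**5. Bias.** Under random order the mean bias between two conditions is about 0, and type I error stays near 0.05 with or without the session term. With a Latin square at N = 30, each condition falls 7 or 8 times in each position. The largest bias is then 0.02 / 0.04 / 0.06 SD for G = 0.5 / 1.0 / 1.5.

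**6. Length of a practice run.** 30 letters × 3.5 s = 105 s per block; × 3 blocks = 315 s; × 2 tasks = 630 s = 10.5 minutes.

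**The case against.** The strongest reply is that the plan already deals with learning. The reason it gives concerns a pre-test in the same session, and omitting that does avoid extra exposures. The next lines of the n-back section promise counter-balancing and an order variable, Statistical analyses adds a look by session sequence, and Limitations admits the problem. The article never claims that learning is absent. This stands, and it limits the harm to precision.

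It also stands that the large losses arise only when order is left out. With order modelled, the rest hangs on the assumed between-person SD. At μ = 1 and τ = 1, 16% of participants would have a negative deficit and so get worse with practice, which makes τ = 1 a demanding assumption. The planned correlation of 0.5 may already include some variation in learning. Adding it on top lowers the implied average correlation to about 0.48, so part of the loss may be counted twice. Each session also has three blocks per task, so block-level data could help to examine early learning.

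A condensed article may leave out a familiarisation run, so none is described, which is not proof that none exists. Spare time at the MRI visit is inferred from the visit list.

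What the reply does not remove is that the stated reason fails for learning between sessions, and that the ANOVA as described does not name the order term promised for it.

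A reader might infer that first-session learning biases the comparison of conditions, or that a practice run is needed to rescue the trial's power. The documents support neither: order is randomised and counter-balanced, and with order modelled the worst simulated power is about 0.82 against a planned 0.85.

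**Conclusion.** The point holds in a limited form. Omitting the pre-stimulation n-back does not avoid learning over four scored administrations, and as described the first exposure is outcome data. This causes no systematic bias. The loss of precision is large only with group as the sole factor: from about 0.91 to 0.80-0.62 at an assumed mean deficit of 1-2 and SD 1 residual SDs. With order in the model it is about 0-2 points at a between-person SD up to 0.5, and about 4-6 points at SD 1.

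The size of learning, its decay and its spread between people are all assumptions, because the article gives no learning data. That the steepest gain falls at the first exposure is plausible but also assumed. Severity: optional, low-cost improvement.

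**What to change.** 1. In Statistical analyses, put the session-order term into the n-back model, so that it agrees with the n-back section. This costs one line of text and 3 error degrees of freedom (87 to 84 at N = 30), and it protects most of the power.
2. In the n-back section, reword the reason so that it claims a reduction of learning effects and not their avoidance.
3. In Procedure and the n-back section, add one full 0-back and 2-back run at visit 1, without stimulation and not used as an outcome, or state that a familiarisation run already exists. The cost is about 10.5 minutes with the existing task program. The downside is a slightly longer first visit, and it depends on time being available on the MRI day.
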